## Background

The smartphone has become indispensable in the lives of most of humankind during the last two decades [1, 2]. More than 75 % of families own mobile devices such as smartphones [3]. Recent statistics from local and national surveys reveal a rapidly increasing trend in the use and possession of smartphones not only among adults but also among children and adolescents [4]. In 2011, 52 % of children below 9 years of age had access to mobile devices; in 2013, that access rate had increased to 75 % [5]. In 2018, about half of the elementary school students in the United State and Europe, possessed their own mobile phone [6]. In 2009, the average screen time of 8- to 18-year-old youngsters was 7.38 h, which is 1.17 h more than the one reported in 1999 [7]. A similar pattern has been observed in Hong Kong. A survey about the use of smartphones among 10- to 24-year-old adolescents and young adults revealed that 88.8 % of the respondents possessed a smartphone [8]. The older the age, the higher the possession rate [1]. The average time spent on screen media increased 15 % in nine years’ time, from 2003 to 2012. In particular, young adolescents aged 10 to 14 years showed the largest increase in screen time. Their average duration spent on screen media per week increased from 14.6 h to 2003 to 18.5 h in 2013 (an increase of nearly 27 %) [4].

The continuously increasing possession and use of mobile devices among children and adolescents is alarming because both their bodies and minds have not yet fully developed; in particular, their self-discipline is weak. The uncontrolled use of these mobile devices will make them even more susceptible than adults to the negative effects of mobile devices on their physio-psycho-social health [1]. Preliminary evidence shows that prolonged engagement with these devices disrupts cognitive development and leads to various physiological and psychosocial problems, including but not limited to visual problems, disruptions of memory, decline of attention, addiction, learning and social problems [1, 9, 10]. Furthermore, breaking addictive patterns early in life will help them maintain the benefits into adulthood. The research team therefore focuses on investigating effective intervention to manage the addictive smartphone behavior of this vulnerable group.

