### Hypotheses

The three primary hypotheses of this study are: (1) the smartphone behavior of adolescents can be improved by participating in a group mindfulness-based cognitive programme; (2) the smartphone addictive symptoms of adolescents can be reduced by participating in a group mindfulness-based cognitive programme; (3) the resilience of adolescents can be increased by participating in a group mindfulness-based cognitive programme. The secondary hypothesis is that socio-demographic characteristics, resilience and smartphone behavior are associated with the symptoms of smartphone addiction in adolescents.

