### Sample size calculation

As it is the first study investigating the effect of the MBCP on smartphone behavior in adolescents, the project team can only decide the predicted intracluster correlation with reference to other studies investigating adolescent behavioral problems. The predicted intracluster correlation of 0.01 is adopted based on studies about smoking prevention and alcohol use in adolescents [55, 56]. 20 % potential dropout/noncompliance rate is considered reasonable. Assuming a Type 1 error of 0.05 and Type II error of 0.2, a total of 240 participants (i.e. 120 in each group, 60 in each school) is required to achieve a medium effect (Cohen’s *d*) of 0.5 [57] for comparing the treatment effect between the two treatment groups and among the measurement points within groups for the three outcomes to be measured – resilience, smartphone behavior and symptoms of smartphone addiction.

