#### Smartphone behavior

Smartphone behavior will be operationalized in terms of duration of daily smartphone use and types of smartphone functions used. Duration of daily smartphone use will be assessed by one closed-ended question - ‘On average, how long do you use your smartphone on a typical day?’. The respondents will respond to the question by choosing among the six categories - ‘less than 10 minutes’, ’11–60 minutes’, ‘1–2 hours’, ‘3–4 hours’, ‘5–6 hours’, or ‘more than 6 hours’. For types of smartphone functions used, the respondents will indicate the frequency of using a specific smartphone function such as social networking, phone calls, gaming, etc. in a 5-point Likert scale (0 = never, 1 = rarely, 2 = sometimes, 3 = usually, 4 = always).

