### Data analysis

IBM SPSS version 23 will be used for statistical analysis. Mean and standard deviation will be reported for continuous variables, i.e. age, types of smartphone functions used and total resilience score. Frequency and percentage will be reported for nominal and ordinal variables. Cronbach’s alpha and intra-class correlation coefficients will be calculated to determine the validities and reliabilities of the two scales: the translated Smartphone Addiction Scale and the Chinese Version of Conner-Davidson Resilience Scale – 25. Independent t-test/Mann-Whitney U test will be used to compare the socio-demographic variables between intervention and control groups. Generalized Estimating Equation model will be used to verify all the hypotheses. The socio-demographic variables will be treated as co-variates to adjust the group means. Results will be reported with 95 % confidence interval. Intention-to-treat analyses will be applied to the independent and dependent variables. Missing data will be handled by replacing the missing values with the item-specific mean. Tests performed will be two-tailed with alpha value set at 0.05. Cohen’s *d*, calculated by taking the difference of the adjusted means between two comparison groups and dividing it by the pooled standard deviation, will be used to estimate the effect size of the treatment.

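### The printed answer options for daily smartphone use leave gaps at 2–3 h and 4–5 h, and the planned Cohen's d is not defined for this ordinal item

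*Protocol article*

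**What the plan says.** Protocol article, Smartphone behavior: the outcome is "operationalized in terms of duration of daily smartphone use and types of smartphone functions used". Duration comes from one question, "On average, how long do you use your smartphone on a typical day", with six answers: under 10 minutes, 11 to 60 minutes, and then "1–2 hours’, ‘3–4 hours’, ‘5–6 hours’, or ‘more than 6 hours". No instruction on rounding is printed.

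Protocol article, Hypotheses: the first of three primary hypotheses is "1) the smartphone behavior of adolescents can be improved by participating in a group mindfulness-based cognitive programme". The primary objective also names smartphone behavior.

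Protocol article, Sample size calculation: the 240 children are justified by a Cohen's d of 0.5 for all three outcomes, smartphone behavior included.

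Protocol article, Data analysis: the effect size is the difference of adjusted group means divided by a pooled standard deviation. Age, function use and the resilience total are listed as continuous; duration is not. For the rest, "Frequency and percentage will be reported for nominal and ordinal variables". GEE is named for every hypothesis, with no link or distribution given.

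Protocol article, Background: for ages 10 to 14, "Their average duration spent on screen media per week increased from 14.6 h to 2003 to 18.5 h in 2013".

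**The concern.** Answer options for a duration should cover every possible value once. These do not. The question asks for an average, so an answer such as two and a half hours is natural, and that child has nowhere to put it. The choice between the band below and the band above is then left to the child, and may differ between visits with no change in use. Face validity and reliability checks are described only for the resilience and addiction scales, so no stated pre-test would catch the problem in this item.

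The second part is a mismatch of scale. Duration is recorded in six ordered bands of unequal width, the last one open-ended, with no numeric score attached. A standardised mean difference has no meaning for such an item until scores are assigned, yet both the power statement and the effect-size definition apply one to smartphone behavior without exception. At stake is the interpretability of one component of a primary outcome, not the whole trial.

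**Working it through.** **1. Coverage of the options.** Setting the six bands end to end:

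- under 10 min, then 11–60 min: only 10 to 11 min is missing, which is trivial;
- 1–2 h, then 3–4 h: more than 2 to under 3 h is missing;
- 3–4 h, then 5–6 h: more than 4 to under 5 h is missing;
- 5–6 h, then more than 6 h: contiguous.

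A child at 2.5 h is 0.5 h from the nearest edge of either neighbouring band.

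**2. Where the protocol's usage figures fall.** From the Background, ages 10–14, all screen media: 14.6 / 7 = 2.09 h per day and 18.5 / 7 = 2.64 h per day. Both lie in the 2–3 h gap and neither in the 4–5 h gap. The Background also says that "the average screen time of 8- to 18-year-old youngsters was 7.38 h". The period is not stated; if it is daily, the figure falls in the top band, outside both gaps.

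**3. How many children could be affected (assumption).** The documents give no standard deviation. Taking gamma or lognormal daily use with SD from 1.0 to 2.5 h:

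| Mean use | Share in 2–3 h | Share in 4–5 h |
|---|---|---|
| 2.64 h/day | about 16–42% | about 6–9% |
| 2.09 h/day | about 12–30% | about 3–6% |

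These shares also assume that the screen-media mean stands in for smartphone use.

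**4. Does the sample size rest on a mean difference?** Inputs from Sample size calculation: "Assuming a Type 1 error of 0.05 and Type II error of 0.2", d = 0.5, ICC 0.01, 60 per school, 20% dropout. The tests are two-tailed (Data analysis).

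- Individually randomised: n = 2(1.960 + 0.842)² / 0.5² = 62.8, so 63 per arm (64 with the t distribution).
- Design effect 1 + (m − 1) × 0.01: 1.59 at m = 60; 1.47 at m = 48 completers (60 × 0.8).
- 63 × 1.59 × 1.2 = 120.2, so 121 per arm, 242 in total.
- 64 × 1.47 / 0.8 = 117.6, so 118 per arm, 236 in total.

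Both are within 3% of 240. Using m = 60 and dividing by 0.8 gives 126 to 128 per arm (252 to 256). With 96 completers per arm and design effect 1.47, the effective number is 96 / 1.47 = 65.3 per arm and power is 81.5%. The stated size is therefore reproduced, and by a two-means formula.

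**5. What d becomes on this item (illustration).** Simulated gamma-distributed use with a mean of 2.64 h in one arm, a true d of 0.50 in hours, 65 effective children per arm, and the six bands scored as consecutive integers:

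| SD of use | Gap answers go down | Nearest | Up |
|---|---|---|---|
| 1.5 h | d = 0.50 | 0.54 | 0.57 |
| 2.0 h | d = 0.63 | 0.65 | 0.68 |

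The same difference in hours gives a different d depending on where gap answers land and on the spread of use. Power of a t-test on the codes did not fall below 80% in any of these scenarios; the lowest was 81.4%.

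**The case against.** Much can be said on the other side.

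- **The usage figure is a weak proxy.** It covers all screen media at ages 10–14 and ends in 2013, whereas the outcome is smartphone use at ages 10–11 with collection planned from September 2020. Smartphone time is only part of screen time, so the same source is compatible with a mean inside 1–2 h. This stands, and limits the point to saying that the 2–3 h gap may be hit often.
- **Children may round to whole hours.** Then every hour option is usable. That is possible, but nothing printed tells them to round, or in which direction.
- **GEE can fit an ordinal outcome**, and the link for each outcome is normally left to an analysis plan that is not shown. This stands: the analysis model is not itself wrong. What remains is the printed d, which is not exempted for this item. Duration's absence from the list of continuous variables is weak evidence alone, because the addiction total is missing there too.
- **d remains usable for the function-frequency items**, which the plan treats as continuous. This also stands.

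A reader might infer more than the documents support: that both gaps sit where the average child is (no average falls in 4–5 h); that rounding moves a child by three hours (that measures the outer edges of two bands); or that children in the intervention arm will round down. The last is conjecture. The trial is open-label and the Discussion concedes possible ascertainment bias, but hypotheses are withheld from teachers, parents and students, and any self-report item carries the same risk.

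**Conclusion.** The point holds in a limited form. The printed options are not exhaustive at 2–3 h and 4–5 h, and no rounding rule repairs this; that needs no assumption. How many children are affected cannot be read from the documents: about 12–42% in the 2–3 h gap under the assumed means, SDs and distributions, and fewer, about 3–9%, in the 4–5 h gap.

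The mean-based Cohen's d is undefined for duration as scored, and in the illustration it moved by about 0.05 to 0.07 with the placement of gap answers alone. It does not follow that 240 is too small: the figure is reproduced within 3%, and no loss of power below 80% appeared. The mismatch concerns duration only; the resilience and addiction totals are numeric. It should be corrected, but it does not undermine the trial as a whole.

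**What to change.** **If baseline has not been collected:** replace the options with contiguous, exhaustive categories, each boundary belonging to exactly one category, or ask for hours and minutes on a typical day. With hours and minutes, a mean and SD exist and d is defined, though skewness should be examined.

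**If baseline has been collected** (possible, since collection was planned from September 2020 and the article appeared in June 2021): keep the same form at every visit, so that baseline and follow-up answers stay comparable.

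**Whenever categories are used:** state that duration will be analysed with a cumulative-logit GEE and reported as an odds ratio with its 95% confidence interval. Limit Cohen's d, and the power statement based on d = 0.5, to the numerically scored outcomes.

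**Cost:** one questionnaire line, one sentence in the analysis section, and a power statement that no longer covers duration. The planned number of children does not change.

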#### Resilience

Resilience will be measured by the Chinese Version of the Connor-Davidson Resilience Scale – 25 [58, 59]. It consists of 25 items reflecting five factors of resilience: (1) tenacity, (2) control, (3) spiritual influence, (4) positive acceptance of changes and secure relationship, and (5) tolerance of negative affect and strengthening effects of stress [58]. Each item consists of statements such as ‘able to adapt to change’, ‘close and secure relationships’, ‘sometimes fate or God can help’, ‘can deal with whatever comes’, etc. The respondents will be asked to rate their agreement with each statement based on their experiences in the previous month. If a particular situation has not arisen in that time, the respondents will be instructed to respond according to how they think they would have reacted. The respondents will be directed to indicate their response on each item with a 5-point Likert scale, 0 is ‘not true at all’ and 4 is ‘true all the time’. The total resilience score ranges from 0 to 100, with higher scores indicating greater resilience. The scale has been applied to various target populations including children 10 years old and above. A Flesch-Kincaid score of 5 indicates that the scale is expected to be understood by those with a fifth-grade level education that is 10 years of age [60]. Thus, the scale is suitable for the target group in this study. Regarding the validity and reliability of the Chinese version, the Cronbach’s alpha coefficient was 0.89. The resilience score had positive correlation with social support (*r* = 0.44) and negative correlations with depression (r=-0.38) and anxiety (r=-0.25) [59]. To ensure the scale is appropriate and comprehensible to class level 5 Hong Kong primary school students, a panel of primary school teachers will be invited to review the scale and make minor modifications in the wordings. Face validity, internal consistency and test-retest reliability will be conducted with 20 adolescents before the actual data collection.

#### Smartphone addictive symptoms

Smartphone additive symptoms will be assessed using the Smartphone Addiction Scale-Short Version. This 10-item self-administered questionnaire was developed by Kwon et al., 2013 based on the original validated Smartphone Addiction Scale [18]. The scale addresses five domains of smartphone addiction: (1) daily-life disturbance, (2) withdrawal, (3) cyberspace-oriented relationship, (4) overuse and (5) tolerance. The respondents will rate their agreement with each item on a 6-point Likert scale, from 1 representing ‘strongly disagree’ to 6, representing ‘strongly agree’. The total addiction score possible ranges from 10 to 60. The higher the score, the more severe the addictive symptoms. The internal consistency (Cronbach’s alpha) was 0.911. Analysis of receiver operating characteristics demonstrated that for boys, the sensitivity was 0.867 and the specificity was 0.893. For girls, the sensitivity and the specificity were 0.875 and 0.886 respectively [18]. A Chinese-version of the scale will be translated based on the English version by backward translation, i.e. a native Chinese and English-speaking teacher. Face validity, internal consistency and test-retest reliability will be conducted by inviting 20 adolescents to fill out the questionnaires before actual data collection, to ensure the translated version is valid and reliable for this study.

### Intervention

The participants allocated to the intervention group will receive a 12-week group mindfulness-based cognitive programme (MBCP) adapted from the MCBT-C developed by Lee et al. (2008) [52]. It consists of two components: weekly 90-minute supervised practice, and daily 15 min home practice. Supervised practice will be conducted in a group of 20 at a quiet room of the primary school. In the first supervised practice session, the trainer will inform the participants the rules of the practice sessions, for example, ‘we can remember not to talk when another person is talking.’, ‘we agree not to talk during mindful awareness practices so as not to disturb others.’, etc.

 Participants will be directed to perform a short breath meditation at the beginning and at the end of each session. To engage the young participants in the session, the trainer, who has years of experience in providing mindfulness and cognitive therapy to children, will use a variety of short sensory-based movement activities that are practiced repeatedly in 3- to 5-minute blocks. These simple sensory exercises can enhance their mindful awareness by helping them to experience internal and external environments non-judgmentally through various senses, i.e. sight, sound, touch, taste, smell and kinesthetic. Examples of these activities are sensory-based practices, seated breath meditations, mindful movement activities, body scans, visualization practices, and drawing and writing [51]. If there are participants with food allergies, the trainer will not select the allergic foods for the eating/smelling/touching activities. The parents will be informed the food that will be used for training in the week before each session in writing.

Aside from the supervised practice, the participants will be introduced to three to four home-practice activities during each supervised session. They will be encouraged to perform these activities for about 15 min a day, six days a week. Each participant will have his/her own logbook labeled with his/her code to record the home practices. The trainer will review the practice record every week. Those who have not performed the home-practice activities will be reminded by the trainer to do them in the coming week to increase the compliance. Details of the mindfulness-based cognitive programme can be found in Table 1.

**Table 1 Tab1:** Mindfulness-based Cognitive Programme. (modified from Semple & Lee, 2011)[61]

Week	Supervised Practices		Home Practices (15 min/day x 6 days a week)
	Session (90 min)	Mindfulness-based cognitive technique	
1	Session 1	- Foster a secure, cohesive group environment devoted to the cultivation of mindfulness - Inform group norms and privacy of participants - Invite children to pair off and introduce themselves - Hand the half-full cup to the next child and not to spill any water - Draw on the front cover of the notebook ‘Mindfulness in Everyday Life’ - Cultivate mindfulness with breathing: Practice mindful breathing - Discussion: the differences between the experiences of mindful breathing and usual breathing	- Mindful breathing lying down - Mindful breathing sitting up - Living with awareness
2	Session 2	- Review home practices from previous session - Practice mindful breathing - Discussion: what is the purpose of practicing mindfulness in life? - Introduce mindful awareness of breath, body sensations and movements: eating, walk around the school hall	- Living with awareness - Mindful breathing - Mindful eating
3	Session 3	- Review home practices from previous session - Practice mindful breathing - Describe thoughts and feelings after hearing a short scene description - Listen the sound of bell ringing and the silence followed - Discussion: what was it like to observe the inside of the body with mindful attention? what did you notice about silence that we might not normally notice?	- Mindful breathing - Mindfulness of the body - Pleasant events
4	Session 4	- Review home practices from previous session - Practice mindful breathing - Enhance awareness to thoughts and feelings associated with food by practicing mindful eating - Understand that thoughts, feelings and body sensations are subjective experience: compare and discuss the differences between the mindful eating and the usual eating experiences - Cultivate mindfulness in body movement: practice several yoga postures	- Three-minute breathing space - Mindful yoga movements - Tasting fruits
5	Session 5	- Review home practices from previous session - Practice mindful breathing - Introduce mindful hearing: listen to music - Discussion: what made us each have different responses to the same piece of music? - Practice awareness to body sensation: pay attention to sensations in the body	- Three-minute breathing space - Mindfulness of the body - Mindful listening
6	Session 6	- Review home practices from previous session - Practice mindful breathing - Practice using sounds to express emotions: Be a conductor to guide the group to create music - Discussion: how is it that we don’t have the same thoughts and feelings when we hear the same thing? - Cultivate mindfulness in body movement: practice several yoga postures	- Three-minute breathing space - Mindful yoga movements - Unpleasant sounds
7	Session 7	- Review home practices from previous session - Practice mindful breathing - Learn to differentiate between judging and noting: practice mindful seeing - Practice mindful body movement: perform several yoga postures - Visualization with clarity: Draw a picture of the phone the children use most often - Discussion: how is seeing from your ‘Mind’s Eyes’ different from seeing with your real eyes?	- Three-minute breathing space - Seeing the little detail - Stressful events
8	Session 8	- Review home practices from previous session - Practice mindful breathing - Learn to shift attention with purpose and intention: practice mindful seeing and discussion - Differentiate descriptive observations with feelings, thoughts and body sensations: practice mindful stretching	- Three-minute breathing space - Choosing to be aware - Seeing five new things
9	Session 9	- Review home practices from previous session - Practice mindful breathing - Deepen awareness of judgement and how judgment influence one’s perceptions of the things we touch: practice mindful touch - Practice awareness to body sensation: pay attention to all sorts of sensations in the body	- Three-minute breathing space - Mindfulness of the body - Mindful touching
10	Session 10	- Review home practices from previous session - Practice mindful breathing - Practice mindful smelling: Smell the scents inside a container and describe it with one adjective - Discussion: reflection on how judgments and emotional reactivity change the nature of experience - Practice mindful body movement: perform several yoga postures	- Three-minute breathing space - Mindful yoga movements - Mindful smelling
11	Session 11	- Review home practices from previous session - Practice mindful breathing and mindful eating - Review of concepts and skills learned in previous sessions - Consolidate insights gained over the past weeks - Understand that beliefs and expectations are often inaccurate: Listen to a four sentence-story and write down what the children think about the story - Understand how emotions affect an interpretation of an event: Listen to a story, see and feel it by imaging themselves as part of it - Draw on the back cover of the notebook ‘Mindful in Everyday Life’	- Three-minute breathing space - Letter to my self
12	Session 12	- Review home practices from previous session - Practice mindful breathing - Discussion: personal experiences in the past 12 weeks; ways to continue to cultivate mindful awareness in daily lives.	------

Over the data collection period, the controls will not exposed to any interventions except counselling services that normally provided to students in need by social workers at the school due to emotional/behavioral issues.

